### Data collection procedure

Data will be obtained by questionnaires. Participants will be asked to return each of the questionnaires within one week. To minimise loss to follow-up, the parents will be called by phone if the questionnaire has not been returned within one week. The outcome assessments will take place, regard for equal time intervals, directly after treatment (T1), six months (T2) and twelve months (T3) after treatment. Parents who complete all questionnaires will receive a gift voucher.

### Analysis

Statistical analysis will be performed according to the 'intention-to-treat' principle. With multiple measurements over time, data on subjects lost to follow-up will be handled by imputation techniques. Change in child behaviour and parenting behaviour will be expressed as standardised effect sizes. To analyse the development of the outcome measures in time, a longitudinal data analysis technique, i.e. random coefficient analysis, will be applied. Baseline characteristics of the parents in the two research groups will be compared using Chi-squared tests for categorical variables, Wilcoxon's test for ordinal variables, and t-tests for continuous variables. Reporting will follow the CONSORT guidelines.

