**Methods/Design:**

The effects of the intervention will be studied in a randomised controlled trial. Prior to a routine PCH health examination, parents complete a screening questionnaire on psychosocial problems. Parents of children with increased but still subclinical levels of psychosocial problems will be assigned at random to the experimental group (Triple P, level 3) or to the control group (care as usual). Outcome measures, such as problem behaviour in the child and parenting behaviour, will be assessed before, directly after and 6 and 12 months after the intervention.

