### Randomisation procedure

At the clinic, a research assistant ensures that participants enrolled by CHPs are eligible or have to be excluded from the trial. Randomisation, based on a computer-generated randomisation programme, occurs at the level of individual children in sequence of entrance. To prevent unequal randomisation, participants are pre-stratified and randomised by centre using block randomisation (blocks of six).

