### Sample size

The SDQ will be the primary outcome measure for the power calculation. For an average 3-point decrease in SDQ total problems score, i.e. a change from the subclinical to the normal range, SD = 6 at alpha = 0.05 (two-sided) and beta = 0.20, 64 pairs of children need to be included with an initial SDQ total problems score between 11 and 13. As a loss to follow-up rate of 20% is expected, an initial study population of 80 pairs of children is needed in each treatment group (total: 160). This suffices to show an effect size of 0.5 of the Triple P programme regarding parent-reported child psychosocial problems and parenting problems.

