### Outcome measures

The primary outcome of the study is problem behaviour of the child after intervention, measured by the (1) Strengths and Difficulties Questionnaire (SDQ) [20], 30 items divided into 5 subscales on prosocial behaviour, hyperactivity, emotional symptoms, conduct problems and peer problems and (2) the Eyberg Child Behavior Inventory (ECBI) [25], 36 items on parental perception of disruptive behaviour including intensity and problem score.

The secondary outcome of the study is parenting behaviour since the intervention aims at parenting as mediator. Parental competence and parenting style will be measured by the (1) Problem Setting and Behaviour Checklist (PSBC) [26], a 28-item rating scale that assesses how confident parents are in dealing with child behaviour problems in various settings and (2) the Parenting Scale (PS) [27], 30 items on parenting behaviour (permissiveness, overreactivity, verbosity). Parenting stress will be measured by (1) the Dutch Parental Stress Index (PSI) [28], 11 items on parenting stress, and (2) the 21-item Depression, Anxiety and Stress Scale (DASS) [29].

At baseline family characteristics will be assessed, i.e.: family situation, age of the parents, parental education, employment and financial situation of the parents, and the ethnicity of the parents and the child.

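### The planned between-arm significance tests of baseline characteristics cannot inform a randomised comparison; baseline should be described by arm, and baseline scores used as prespecified covariates (minor)

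*Protocol article*

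**What the plan says.** The Analysis section of the protocol article fixes the method: "Baseline characteristics of the parents in the two research groups will be compared using Chi-squared tests for categorical variables", followed by "Wilcoxon's test for ordinal variables, and t-tests for continuous variables". The characteristics are listed under Outcome measures: "family situation, age of the parents, parental education, employment and financial situation of the parents, and the ethnicity of the parents and the child". The Randomisation procedure section states: "Randomisation, based on a computer-generated randomisation programme, occurs at the level of individual children", stratified by centre in blocks of six.

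Outcome scores are also collected before treatment. The abstract says: "Outcome measures, such as problem behaviour in the child and parenting behaviour, will be assessed before". The Analysis section reports change in child and parenting behaviour as standardised effect sizes and models development over time by random coefficient analysis. It lists no covariates and does not say what will follow from a significant baseline test.

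**The concern.** A significance test asks whether a difference could be chance. After computer allocation carried out as described, the answer is known beforehand: it is chance. A small p-value therefore says nothing about the treatment comparison. A large one does not reassure either, because the effect of an imbalance depends on its size and on how strongly the variable predicts the outcome, and the test ignores the second.

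Two things are at stake. Readers may be shown chance differences as if they were real differences between the groups, and analysts may be tempted to adjust for whatever reached significance. Separately, if baseline scores enter only through change, some precision may be given up on the scales whose baseline spread is not cut off by the entry criteria.

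**Working it through.** **The plan's own figure.** The Sample size section gives "For an average 3-point decrease in SDQ total problems score" and "SD = 6 at alpha = 0.05 (two-sided) and beta = 0.20".
- Normal approximation: n = 2(1.96 + 0.8416)² × 6²/3² = 62.8, so 63 per arm.
- The exact two-sample t calculation gives 64 per arm (power 80.1%), and 64/0.80 = 80 per arm. The stated figures reproduce, reading the stated 64 pairs as 64 per arm.

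**Chance of at least one significant baseline test.** A plain count of the listed characteristics gives seven. It is six if the child's ethnicity is left out, since the Analysis section speaks of the parents. The article states 5% for the power calculation only; its use here is an assumption.
- Seven independent tests: 1 − 0.95⁷ = 30.2%.
- Six independent tests: 1 − 0.95⁶ = 26.5%.
- Seven tests with a common correlation of 0.3 or 0.5 (simulated): about 27% or 23%. Six correlated tests would lie a little lower.

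**A non-significant test does not mean a harmless imbalance.** Let ρ be the correlation of a covariate with follow-up SDQ (not given in the article; assumed) and z its standardised imbalance between arms.
- Shift in the SDQ difference: ρ × z × 6 × √(2/64). With ρ = 0.5 and z = 1.5 (baseline p = 0.13) this is 0.80 points, against the 3 planned.
- Conditional type I error of the unadjusted comparison: P(|N(ρz, 1 − ρ²)| > 1.96).

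| ρ | z = 1.5 (p = 0.13) | z = 1.9 (p = 0.06) |
|---|---|---|
| 0.5 | 8.2% | 12.2% |
| 0.3 | 6.2% | 7.7% |

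With ρ = 0.5 and z = 0 the same formula gives about 2.4%. These are errors given a particular imbalance; averaged over all randomisations the error stays at its nominal level.

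**Change score against baseline adjustment.** With equal variances and pre-post correlation r (assumed), the variance is proportional to 2(1 − r) for a simple change score and to 1 − r² after adjustment.

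| r | Change, 2(1 − r) | Adjusted, 1 − r² | Reduction |
|---|---|---|---|
| 0.5 | 1.00 | 0.75 | 25% |
| 0.6 | 0.80 | 0.64 | 20% |
| 0.7 | 0.60 | 0.51 | 15% |

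This concerns the ECBI, PSBC, PS, PSI and DASS, on which the entry criteria set no score limits.

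**Baseline SDQ as a covariate.** Entry at 11-13 gives a baseline SD of at most 1.0 (0.82 if uniform). With an assumed slope of 0.5 to 1.0 on follow-up and SD 6, the correlation is slope × baseline SD/6:
- lowest: 0.5 × 0.82/6 = 0.07;
- highest: 1.0 × 1.0/6 = 0.17.

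By normal approximation, power at 64 per arm moves from 80.7% to between 80.9% and 81.8%, a gain of about 1 point or less.

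**Other covariates for the SDQ.** If they explain 10%, 20% or 30% of follow-up variance (assumed), the residual SD is 6√(1 − R²), and exact t power at 64 per arm goes from 80.1% to 84.1%, 88.1% or 91.8%.

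**The case against.** The strongest reply is that the tests are descriptive. They leave the treatment comparison, its estimand and the validity of the primary analysis untouched. That stands, and it limits the point to a minor one.

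Several stronger readings are tempting, and the article does not support them:
- **Baseline data serve only for these tests.** This is not so. Pre-intervention outcome scores enter through change and the longitudinal model. Testing is the only role stated for the family characteristics.
- **Test results will choose the covariates.** No sentence says so. The risk is that the tests invite it.
- **The lack of a covariate list is a defect.** A condensed article commonly leaves this to the full protocol or analysis plan, so its absence is no finding.
- **The plan analyses change scores and so loses 15% to 25% in precision.** Change is named as the way effects are expressed, whereas the named analysis is a random coefficient model. The percentages apply to a simple change score. The loss in the planned model may be smaller or nil, depending on how baseline enters it.
- **Type I error is inflated.** Not overall. The 8.2% and 12.2% are conditional on unfavourable imbalances and an assumed correlation.
- **Adjustment would raise power at no cost.** No prognostic strength is given, and covariates cost degrees of freedom and need handling when missing.

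It can also be objected that baseline ECBI is not clearly collected. The abstract has problem behaviour measured before the intervention. The Recruitment section, however, names only the SDQ screen and an added questionnaire on parenting behaviour. This stands as a condition on the fix.

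**Conclusion.** The point holds as a minor one. The article fixes a method that cannot inform a randomised comparison and that would show at least one chance finding in roughly 23% to 30% of trials. That range assumes a 5% level, six or seven tests, and correlations from nil to moderate.

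For the scales not truncated by entry, adjusting for their own baseline is more precise than a simple change score, by 25%, 20% or 15% in variance at assumed correlations of 0.5, 0.6 or 0.7; what this trial would gain depends on how its model treats baseline. For the SDQ, its own baseline adds almost nothing. The gain from other covariates is uncertain: power reaches 84% to 92% only if they explain an assumed 10% to 30% of variance. Nothing here makes the primary analysis invalid as written.

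**What to change.** In the Analysis section:
- Delete the between-arm baseline tests and describe baseline by arm (number, mean and SD, or percentage).
- In the random coefficient model, adjust ECBI, PSBC, PS, PSI and DASS each for the same scale's baseline value.
- Include centre, the randomisation stratum.
- For the SDQ, prespecify another baseline score, such as ECBI intensity, provided it is measured before the intervention.
- State that no covariate is added or dropped because of a baseline p-value.

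This takes a few sentences. It costs a few degrees of freedom and a rule for missing covariate values. No new data are needed if baseline ECBI is collected as the abstract implies; that should be confirmed first.

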### Time frame of the study

The preparatory period will take six months. In this period, nurses will be trained to carry out the intervention (Triple P, level 3). Furthermore, CHPs will be trained in recruiting potential participants in the trial. The inclusion phase will last two years and the follow-up phase will be twelve months. Analysing data and reporting the findings will last for six months. Therefore, the total duration of the study will be four years.

## Discussion

This paper presents the design of a randomised controlled trial to investigate the effectiveness of a parenting programme (Triple P level 3) for parents of children with psychosocial problems after an initial, evidence based screening in routine PCH. Research on the effectiveness of interventions in routine PCH is very scarce [8] and no previous trial has been accomodated in a further evidence-based procedure.

Studying the effects of this intervention is important as it aims (1) to reduce the burden of disease of psychosocial problems in children [4,5] and (2) to contribute to the use of evidence-based care for children with psychosocial problems. Furthermore, introducing an evidence-based programme may lead to a more recognisable and consistent approach to parenting support by the PCH.

This short intervention can be easily embedded in the regular procedure. If CHPs suspect parenting problems or behavioural problems in children due to incompetent parenting, they can offer help to parents in three extra contacts as is customary. If Triple P level 3 proves to be effective, this will be conducive to further implementation. CHPs as well as parents of children with mild problem behaviour may benefit from a structured approach to working on and solving problem behaviour in young children. If proven effective, level 3 of the Triple P programme in combination with an available evidence-based detection of psychosocial problems in children may lead to a comprehensive evidence-based method to reduce the burden of disease due to psychosocial problems. Governmental organisations and policymakers may use the results of this study to develop future policy concerning parenting support provided by community healthcare workers.

### Strengths and limitations

A randomisation procedure is applied to reduce the risk of selection and allocation bias. Since participants do not know each other, mutual influencing is considered unlikely. A broad array of outcome measurements gains insight into the treatment effect in many areas of parenting and child behaviour. Furthermore, this study is original in evaluating the effectiveness of an intervention on parenting support in a preventive healthcare organisation (i.e. the Dutch PCH) delivered with regular staff from multiple centres. While the intervention will be carried out in the daily PCH practice, conclusions can be generalised without reservations which makes the external validity of the trial strong. The intention-to-treat analysis gives the trial high internal validity. Contrary to earlier studies, in this research the long-term effects will be assessed by measurements after twelve months after treatment.

There are also some limitations. This study does not provide an independent, professional evaluation of psychosocial problems in children apart from parental judgement. However, parental concerns are a good indicator of problems indentified by professional [30] and observational research is difficult to objectify. Furthermore, the effects of the intervention may depend on the CHPs affinity for parenting support and treatment adherence. Assessment of the effects of parenting support at the level of independent health care workers within this study would be to laborious.

The results of this study will become available in 2012.
